### Trial design

This is a randomized, investigator-blinded, double-armed, parallel-group, phase I/IIb study consisting of two different sub-studies recruiting simultaneously:Second trimester placental transfer study (sub-study 1)The primary outcome of this sub-study is the fetal plasma sildenafil level after oral administration maternally. Fetal plasma will be obtained by fetal cardiocentesis or cordocentesis, required for administration of the drugs used for feticide at the time of pregnancy termination [31, 32]. Maternal blood sampling will be performed simultaneously via peripheral venous puncture.Secondary endpoints are:Doppler ultrasound measures of pulmonary vasodilatation: change in the acceleration time/ejection time (AT/ET) ratio of the main fetal pulmonary artery and of the pulmonary artery branch closest to the ultrasound probe between baseline and the time of fetal blood sampling. Additional measures of blood flow resistance in the fetal main pulmonary artery and in the right and left pulmonary artery branch (Pulsatility Index, Resistance Index, peak systolic velocity, peak early diastolic reversed flow) will also be collectedEffect of sildenafil on the fetal systemic circulation: change in the Doppler waveform of the umbilical artery, between baseline and blood samplingSimulated maternal and fetal pharmacokinetic profilesMaternal tolerance, measured as change in blood pressure, heart rate and oxygen saturation compared to baseline, and incidence of side effects, including any kind of visual disturbanceThird trimester placental transfer and safety study (sub-study 2)The primary endpoint is sildenafil transfer at term, expressed as a ratio of the neonatal over the maternal sildenafil plasma concentration. Neonatal venous blood samples will be collected from the umbilical cord at delivery. Maternal blood sampling will be performed via peripheral venous puncture.Secondary endpoints are:Doppler ultrasound measures of pulmonary vasodilatation as described aboveEffect of sildenafil on the fetal systemic circulation: change from baseline in the Doppler waveform of the umbilical artery, mean cerebral artery, ductus venosus, change in fetal heart rate monitoring patternEffect of sildenafil on the maternal placental circulation: change from baseline in the Doppler waveform of the uterine arteriesSimulated maternal and fetal pharmacokinetic profilesMaternal tolerance measured as change in blood pressure, heart rate and oxygen saturation compared to baseline, and incidence of side effects, including any kind of visual disturbanceNeonatal tolerance, measured as trend in mean arterial blood pressure during the first 24 h of life, vasoactive inotropic score [33] at 24 h of life and early (< 24 h) lung function, expressed as Oxygenation Index and alveolar-arterial oxygen gradient

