
For both sub-studies, participants will be randomized to one of two parallel groups receiving different doses of sildenafil (sildenafil 25 or 75 mg). No placebo control is foreseen. The protocol follows the Standard Protocol Items: Recommendations for Interventional Trials (SPIRIT) recommendations for interventional trials (Additional file 1). 

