### Interventions

In both sub-studies, sildenafil tablets will be administered orally to the mother as this administration route is the most practical and clinically most acceptable for sustained administration, especially in pregnant women. The half-life of sildenafil after oral administration is about 4 h [34]. Therefore, the most commonly used administration schemes for chronical conditions even in pregnancy consist in three administrations daily [20, 35–37].

Two sildenafil doses have been selected according to previously published literature and to our ex-vivo data on placental transfer [30], i.e., 25 and 75 mg. A dose of 25 mg three times daily has been proven safe in the treatment of pregnancies complicated by intrauterine growth retardation (IUGR) [24]. A dose of 75 mg three times daily is the maximum dose used in a trial on pregnant women affected by pre-eclampsia, without any fetal or maternal side effects being reported under that dose [23].

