#### Second trimester placental transfer study (sub-study 1)

A single administration of sildenafil is planned before maternal and fetal blood sampling. Participants will be randomized to receive either a 25-mg or a 75-mg dose. For each dose, participating women will additionally be randomized to receive sildenafil either 2 h or 8 h before the termination. These time points have been selected because they represent the peak time and the trough time, respectively [34].

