### Statistical analysis plan

For all pharmacokinetic, demographic, safety and efficacy outputs, data will be summarized by sub-study and dose group. For continuous variables, summary statistics will include the number of observations, the arithmetic mean, median, arithmetic standard deviation, minimum and maximum. For categorical variables, frequency counts and percentages will be used.

The measured sildenafil concentrations will be used to develop a physiologically based pharmacokinetic (PBPK) model allowing prediction of the maternal dose that will result in therapeutic concentrations in the fetus [43]. The effect of covariates (gestational age, maternal height and weight) will also be assessed.

For efficacy and tolerability endpoints, baseline is defined as the last value for each assessment prior to the subject’s first dose. Each individual change from baseline will be calculated by subtracting the individual subject’s baseline value from the value at the time point. The individual subject’s change from baseline values will be used to calculate the mean change from baseline. Missing values will not be imputed.

Adverse events will be summarized for each of the sub-studies and of the dose groups. Summaries will include the number of patients who have at least one occurrence of the adverse event. In addition, the total number of adverse events with a first reporting of the event while on treatment will be displayed. The analysis will be for descriptive purpose only and no inferential testing was performed.

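### The Doppler effect is planned as a mean change from baseline per dose group, which mixes drug and visit effects and pools the randomised 2 h and 8 h women; the randomised dose difference should be stated with its interval

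*Protocol article*

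**What the plan says.** The Objectives section lists the effect of sildenafil on the fetal pulmonary circulation as a secondary objective. Under Trial design, the leading Doppler endpoint of sub-study 1 is the "change in the acceleration time/ejection time (AT/ET) ratio of the main fetal pulmonary artery", and of the branch nearest the probe, from baseline to fetal blood sampling. Sub-study 2 uses the same measures. The same section states: "No placebo control is foreseen".

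Dose (25 or 75 mg) is randomised in both sub-studies. In sub-study 1 time is randomised too: "For each dose, participating women will additionally be randomized to receive sildenafil either 2 h or 8 h before the termination". The reason given for the two times is that "they represent the peak time and the trough time, respectively".

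The Statistical analysis plan section groups all outputs by sub-study and dose group; sampling time is not named. For efficacy and tolerability endpoints, baseline is the last value before the first dose, and the individual "change from baseline values will be used to calculate the mean change from baseline". Measured concentrations are assigned to a physiologically based pharmacokinetic model. The section names no difference between doses, no contrast between 2 h and 8 h, and no relation of Doppler change to concentration. The Discussion says the trial will give first data on the drug's effect on the fetal pulmonary circulation, ahead of a phase III study.

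**The concern.** Without an untreated arm, the mean change in a dose group is the sum of two things: the drug effect, and the change that would have occurred anyway between the two occasions. The second part can include fetal state, maternal stress or medication around the termination, ultrasound repeatability and regression to the mean. More women make the sum more precise but do not separate its parts.

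The design does contain contrasts in which a visit effect common to the arms cancels, because dose is randomised in both sub-studies. In sub-study 1 the planned grouping averages peak and trough women within each dose, so a response seen only near the peak would be diluted. At stake is how the first data on fetal pulmonary effect are read when phase III is designed.

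**Working it through.** **Inputs from the document.** Sub-study 1: six women per dose and time, 6 × 4 = 24, with a possible stop at 4 × 4 = 16. Sub-study 2: 6 × 2 = 12. On kinetics: "The half-life of sildenafil after oral administration is about 4 h". The article gives no SD, effect size or precision for any Doppler endpoint and states that no formal power calculation was made. There is therefore no Doppler figure to reproduce, and results below are in SDs of the individual change.

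**Assumptions.** Levels are proportional to dose. The 4 h half-life applies to fetal levels (range shown: 3 to 6 h). The SD is equal across groups.

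**1. What the stated mean estimates.** Let v be the visit effect and e(d, t) the drug effect at dose d and time t. The sub-study 1 mean for dose d has expectation v + [e(d, 2 h) + e(d, 8 h)]/2. The within-time difference has expectation e(75, t) − e(25, t). Here v cancels, even if v differs between 2 h and 8 h.

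**2. Size of the risk in reading the mean as effect.** Take no drug effect, a drift of δ SD, and a one-sample t interval with noncentrality δ√n. The chance that the 95% interval excludes zero is:

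| δ | n = 6 (sub-study 2 dose group) | n = 12 (sub-study 1 dose group) |
|---|---|---|
| 0 | 5% | 5% |
| 0.25 | 8% | 12% |
| 0.5 | 17% | 35% |
| 0.8 | 36% | 71% |

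The drift values are assumed; the document gives none.

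**3. What pooling over time mixes.** The 2 h to 8 h ratio is 2^(6/4) = 2.83. Relative exposures are 0.35 (25 mg, 8 h), 1.00 (25 mg, 2 h), 1.06 (75 mg, 8 h) and 3.00 (75 mg, 2 h), a range of 3 × 2.83 = 8.5-fold. For half-lives of 6 to 3 h the range is 6- to 12-fold. Each dose group spans 2.8-fold, and 25 mg at peak nearly equals 75 mg at trough. Dose carries (ln 3)² / [(ln 3)² + (ln 2.83)²] = 1.207/2.288 = 53% of the variance of log exposure (39% to 72% for half-lives of 3 to 6 h).

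Pooling also inflates the SD. If the 2 h and 8 h means differ by 1 SD, the SD within a dose group rises to about √(1 + 1/4) = 1.12.

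**4. Precision of the randomised dose difference.** Half-width = t(0.975, 2n − 2) × √(2/n), with n per dose:

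| Comparison | 95% half-width (SD) | Difference detectable with 80% power (SD) |
|---|---|---|
| Sub-study 1, 12 v 12 | 2.074 × 0.408 = 0.85 | 1.20 |
| Sub-study 1 after a stop, 8 v 8 | 2.145 × 0.500 = 1.07 | 1.51 |
| One sampling time, 6 v 6; also sub-study 2 | 2.228 × 0.577 = 1.29 | 1.80 |
| One sampling time after a stop, 4 v 4 | 2.447 × 0.707 = 1.73 | 2.38 |

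Stratifying 12 v 12 by time costs one or two degrees of freedom and leaves 0.85 unchanged to two decimals.

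**5. Precision of an exposure slope, sub-study 1.** On the log2 scale the groups lie at 0, 1.5, 1.585 and 3.085, with mean 1.5425. The sum of squares is 6 × 4.762 = 28.57 for 24 women and 4 × 4.762 = 19.05 for 16. Half-width per doubling is 2.074/√28.57 = 0.388 SD and 2.145/√19.05 = 0.491 SD. Over the whole range (× 3.085) this is 1.20 and 1.52 SD. These figures use nominal group exposures, not measured levels.

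**The case against.** The strongest reply has four parts.

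- **The plan is descriptive.** No Doppler test is stated, power is disclaimed, and only first data are promised. Nothing says that a non-zero mean change will be credited to sildenafil. This stands, although the sentence limiting the analysis to description follows the adverse-event text and its scope is unclear. A descriptive estimate should still target the effect named in the objective.
- **The dose contrast is already within reach.** Number, mean and SD are to be given by dose group, so a reader can form the 75 minus 25 mg difference and its interval. This also stands. One might infer that the objective cannot be answered at all as planned, but the dose-group reporting does not support that. What is missing is the stated difference, its interval and the split by time.
- **An exposure-response model may sit in a document not shown.** That is fair, so the absence of a slope is not itself the fault. One might also infer that concentrations are reserved for the pharmacokinetic model alone, but the text does not say so. The fault lies in the estimator and grouping that the article does state.
- **The gradient is weak.** A reader might infer that randomised doses and times could settle the question without a placebo. The numbers do not support that. There is no zero exposure, so a flat gradient cannot separate no effect from a plateau. Measured concentration is not randomised and may vary with gestational age (20.0 to 32.6 weeks in sub-study 1), which may itself affect Doppler. Time from baseline to reading may also differ between the 2 h and 8 h groups. The time contrast exists only in sub-study 1, whose women carry fetuses with anomalies not interfering with lung development; the diaphragmatic hernia sub-study has dose alone.

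**Conclusion.** The point holds in a limited form. The stated mean change confounds drug effect with visit effect in every dose group, and in sub-study 1 its grouping averages over a randomised factor that the article itself describes as peak and trough. The randomised dose difference within sampling time is free of a visit effect shared by the two doses and is the cleaner estimate. It would be known to about ±0.85 SD with 24 women, ±1.07 SD after a stop at 16, and ±1.3 SD within one sampling time or in sub-study 2.

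These half-widths depend only on group sizes and an equal SD. The 8.5-fold exposure range and the slope figures rest further on proportional levels and on a fetal half-life that the document does not give. The drift rates rest on assumed drifts. None of this turns the trial into a test of drug against no drug.

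**What to change.** Add a paragraph to the analysis wording for the Doppler endpoints:

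1. Sub-study 1: report change from baseline by the four dose-by-time groups, and estimate the 75 minus 25 mg difference stratified by sampling time, with a 95% interval. Show the difference at 2 h and at 8 h as well.
2. Sub-study 2: report the randomised dose difference with its 95% interval.
3. Label as exploratory the slope of Doppler change on log measured concentration: the fetal level in sub-study 1, and the maternal 50 h level against the 50 h Doppler change in sub-study 2. Consider adjusting for gestational age.
4. State that the within-group mean change is not interpreted as the effect of sildenafil, and that a flat dose difference or slope does not exclude an effect common to both doses.

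No patient, visit or sample is added. In sub-study 1 Doppler and fetal blood are already taken together, and in sub-study 2 the 50 h Doppler and maternal sample coincide. The cost is a more modest claim: intervals are wide and only large dose-related differences can be detected.

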## Discussion

The mortality from CDH-related PHT unresponsive to medical therapy remains around 60% [44], and infants with PHT require prolonged mechanical ventilation, need extracorporeal life support, or progress into right-sided heart failure [44, 45]. PHT also adversely affects the quality of life in CDH survivors [46]. CDH, certainly when complicated by PHT, also is a serious socio-economic burden. The postnatal management costs of a CDH patient is estimated to exceed US$200,000 [47], making it the costliest non-cardiac birth defect [48]. When the baby also has PHT, costs are significantly higher. For instance, when extra-corporeal membrane oxygenation is used (which is more likely in cases of PHT), in-hospital costs rise fourfold. To this, the burden of chronic PHT must be added [49]. Chronic PHT is associated with an increased risk of death, cardiac and pulmonary complications and re-hospitalization. It requires chronic medical treatment, an intense clinical follow-up often with additional testing and investigations.

Therefore, effective treatment or prevention of PHT is urgently needed. SToP-PH introduces the concept of a medical approach that acts already during fetal life hence preventing the ill-development of pulmonary vasculature. The herein described phase I studies are required to properly design a randomized controlled trial on maternal sildenafil administration for the prevention of PHT in CDH. If proven effective, oral administration of a safe drug will also allow for a wider implementation than fetal surgery, including in less privileged countries. Furthermore, sildenafil is generically available. Therefore, this would be the first affordable therapy for a fetal surgical condition ever.

The European Commission has supported the establishment of virtual thematic networks across Europe (European Reference Networks), aimed at sharing knowledge, exchanging information and facilitating collaborations between specialized centers. “ERNICA” is the European reference network on rare diseases of the foregut grouping skills from 20 centers in 11 countries. It covers malformations of the digestive system, the diaphragm (including CDH) and the abdominal wall. Such network will make a randomized clinical trial on CDH fetuses possible, despite the rarity of the condition. We also have already obtained Orphan Designation for this indication by the European Medical Agency (http://www.ema.europa.eu/docs/en_GB/document_library/Orphan_designation/2017/07/WC500231579.pdf). The present phase I/IIb trial should allow to determine the effective maternal dosage to be used in the subsequent phase III efficacy study. Moreover, it will investigate and provide first data on maternal and fetal tolerance and on the effect of the drug on the fetal pulmonary circulation. This knowledge will provide safety information also for other maternal and placental diseases, for which sildenafil is currently being explored.

## Trial status

### Recruiting

Approved by the Belgian National Authorities: 20 July 2017.

Date of local Ethics Committee approval (Leuven): 22 September 2017 (protocol version 5, dated 28 July 2017).

Recruitment starting date: 1 February 2018.

## Abbreviations

AT/ET: Acceleration time/ejection time ratio
CDH: Congenital diaphragmatic hernia
NO: Nitric oxide
PHT: Pulmonary hypertension
TO: Tracheal occlusion
